### Procedure

When contact details of eligible people are received through the Qualtrics survey, a project officer will make contact by phone to verify the information provided, make sure they are aware of and understand all study requirements and that they still agree to participate. Subsequently, they will be e-mailed a link to access to an online baseline survey (administered via Qualtrics). Participants will also be sent an accelerometer-based activity monitor using registered mail, as well as instructions on how to use the device, a 7-day monitoring log and a pre-paid return post bag. They will be asked to wear the activity monitor on the non-dominant wrist for 7 consecutive days and nights from the day of receipt. When the accelerometer is returned to the laboratory, it will be checked for valid wear time. Potential participants providing less than four valid monitoring days (≥ 10 h of wear time) will be excluded from the study. The same measurement procedures (online survey and 7-day accelerometer) will be repeated at 3 and 6 months (though participants with incomplete data will not be excluded at this stage). Participants will be rewarded with a $50 AUD shopping voucher for each completed assessment. Participants can withdraw from the study without any consequence at any stage. Whenever needed, reminder e-mails and phone calls will be used to encourage participants to complete assessments.

In accordance with the approved study data management plan (DMP_2790), data from all sources will be securely stored for a minimum of 10 years on a university server dedicated to research data and regularly backed up. Only study investigators named on this publication will have access to the final trial dataset. Given the small scale of this study, no data monitoring committee will be established beyond the involvement of the study investigators named on this publication. Participants’ identity will be protected at all times; only de-identified and aggregated data will be disseminated in publications and reports. A plain English statement summarising trial outcomes will be shared with participants that indicated an interest. Publications resulting from this study will abide by ICMJE authorship guidelines and not involve professional writers.

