### Measures

#### Primary outcome

Device-measured moderate-to-vigorous physical activity: Participants will be asked to wear an Axivity AX3 tri-axial accelerometer (https://axivity.com/product/ax3) on their non-dominant wrist for 7 consecutive days during waking and sleeping hours, except when swimming, bathing or participating in contact sports. Participants will also be asked to complete an activity monitor log detailing times the monitor was removed, time they went to bed and wake up time. The Axivity AX3 has demonstrated good concurrent validity [36].

Raw accelerometer data collected at 50 Hz will be processed into physical activity metrics using a machine-learned random forest classifier specifically designed and validated for assessing movement behaviours in free living adults [37]. The random forest classification model uses features in the raw acceleration signal to classify each 10-s window (epoch) as sedentary (lying or sitting still), stationary plus (active sitting, standing still, active standing), walking or running. Daily time spent in moderate-to-vigorous intensity physical activity (MVPA) will be calculated using the approach established by Ahmadi et al. in their analysis of accelerometer data from the UK biobank study [38]. Windows classified as walking with normalised gravitation units (milli g) ≥ 100 milli g and < 400 milli g will be considered moderate intensity physical activity (3–6 METs). Windows classified as walking with normalised gravitational units ≥ 400 milli g will be considered vigorous intensity physical activity (≥ 6 METs), while all windows classified as running will be considered vigorous intensity physical activity (≥ 6 METs). Non-wear periods will be identified and differentiated from sleep using the methods described by Ahmadi and colleagues [39]. The participants’ accelerometer data will be included in the analyses if they have ≥ 4 days (with at least 1 weekend day) in which daily wear time is ≥ 10 h [40]. Device-measured physical activity will be reported as the average minutes of MVPA per day or week for each time point and group.

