### Sample size

Sample size for the study is based on the primary outcome of change in device-measured MVPA (min/day). Several reviews of app-based physical activity interventions suggest that most studies have small to medium effects on change in physical activity and have high dropout rates, up to approximately 30% [64, 65]. Hence, to detect a small to medium difference in the change in daily MVPA between groups (*d* = 0.45; corresponding with a minimal detectable difference of 10 min/day), at the study’s primary time point of 6 months, 76 participants per group will be required to achieve 80% power using an alpha level of 0.05. The number of participants per group will be inflated by 30% (99 participants per group) to account for drop out. Hence, a total of 198 participants will be recruited into the RCT.

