### Statistical analyses

Data will be analysed by a statistician blinded to group allocation, using generalised linear mixed models (GLMM), including fixed effects for group, time, the group-by-time interaction and a random subject effect [66]. GLMM analyses examine changes from baseline to each follow-up time point for each intervention group compared to the control group while accounting for within-person nesting of variables across time [66]. Random effects mixed modelling will also be used to explore potential changes in secondary outcomes. Planned subgroup analyses include examining any moderating effects of sociodemographic variables (e.g. sex, age, income) and app usage as potential mediator for increases in physical activity levels. Data will be tested for linearity and normality to ensure the proper statistical techniques are applied. The most appropriate approach to handling missing data will be applied depending on the pattern and amount of the missing data. However, if possible, intention-to-treat including all participants with valid baseline data and multiple imputation by chained equations will be used to handle missing data [67]. The analyses will be conducted using SPSS v30.

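### The entry check, the wear-time rule and the conditional intention-to-treat set do not fit together, so a participant randomised on four valid weekdays can be left out of the primary analysis

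*Protocol article*

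**What the plan says.** Four places in the protocol article bear on this.

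- **Statistical analyses, missing data.** "The most appropriate approach to handling missing data will be applied depending on the pattern and amount of the missing data". The next sentence reads: "However, if possible, intention-to-treat including all participants with valid baseline data and multiple imputation by chained equations will be used to handle missing data". The article does not say what would make this impossible, or which analysis set would then apply.
- **Statistical analyses, model.** The data are to be analysed "using generalised linear mixed models (GLMM), including fixed effects for group, time, the group-by-time interaction and a random subject effect". The same section states: "Data will be analysed by a statistician blinded to group allocation".
- **Procedure.** Before randomisation, "Potential participants providing less than four valid monitoring days" are excluded, a valid day being one with at least 10 hours of wear. There is no weekend condition. Participants with incomplete data at 3 or 6 months stay in the study.
- **Primary outcome.** Accelerometer data enter the analyses only with at least four days of at least 10 hours, "with at least 1 weekend day".

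Under Sample size, the plan notes that most comparable app studies "have high dropout rates, up to approximately 30" per cent, and it inflates recruitment on that basis.

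**The concern.** The wear rule for entering the trial is looser than the wear rule for having data analysed, and the intention-to-treat set is defined by valid baseline data. Read together, the three rules allow a correctly randomised person to be removed from the primary analysis for failing a condition that was not checked at entry.

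Separately, intention-to-treat is a preference that may be set aside, with no stated trigger. The condition serves no purpose. A mixed model uses every observed value, and chained equations can fill in the rest, so nothing in the design makes an analysis of all randomised participants impossible.

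At stake are the completeness of the randomised comparison for device-measured MVPA at 6 months, some precision, and a clear answer to who is in the primary analysis. The plan may leave the variables in the imputation model, and similar detail, to an analysis plan that is not shown. That is not part of this point. The point concerns what the article itself states.

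**Working it through.** **The plan's own figures.** The point disputes none of them. With d = 0.45, two-sided alpha 0.05 (assumed, as sidedness is not stated) and 80% power, the normal formula gives n = 2 × (1.96 + 0.842)² / 0.45² = 77.5, so 78 per group. The stated 76 is within two of this. Then 76 × 1.30 = 98.8, so 99 per group and 198 in total. The figure of 198 is used below.

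**The rules side by side.**

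| Baseline wear | Entry check (Procedure) | Data rule (Primary outcome) |
|---|---|---|
| Fewer than 4 valid days | Excluded before randomisation | Fails |
| 4 or more valid days, at least one at a weekend | Randomised | Passes |
| 4 or 5 valid weekdays, no valid weekend day | Randomised | Fails |

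Only the third row is a problem. Seven consecutive days always include both weekend days, so a participant falls there only if both are invalid and at least four of the five weekdays are valid.

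**How many.** The documents give no validity rates, so these are assumed. Let a weekday be valid with probability p, a weekend day with probability w, and days be independent.

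Share affected = P(at least 4 of 5 weekdays valid) × (1 − w)² / P(at least 4 of 7 days valid)

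Worked case, p = w = 0.80:

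- P(at least 4 of 5) = 5 × 0.8⁴ × 0.2 + 0.8⁵ = 0.4096 + 0.3277 = 0.7373
- (1 − 0.80)² = 0.04, so the numerator is 0.0295
- P(at least 4 of 7) = 0.9667
- Share = 0.0295 / 0.9667 = 3.1%, and 198 × 0.031 is about 6 people

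| Weekday validity p | Weekend equal (w = p) | Of 198 | Weekend 15 points lower | Of 198 |
|---|---|---|---|---|
| 0.80 | 3.1% | about 6 | 9.6% | about 19 |
| 0.85 | 1.9% | about 4 | 7.7% | about 15 |
| 0.90 | 0.9% | about 2 | 5.8% | about 11 |
| 0.95 | 0.2% | about 0.5 | 3.9% | about 8 |

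The right-hand columns only show sensitivity. No section of the article supports a 15-point weekend drop.

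**Cost in precision.** The standard error scales with 1/√n, so losing k of 198, spread evenly over the arms, multiplies it by √(198 / (198 − k)). For k = 6 this is √(198/192) = 1.016, an increase of about 1.6%. For k = 19 it is √(198/179) = 1.052, about 5%.

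**Direction of bias.** The baseline monitoring week is completed before randomisation. Whether a person falls in the third row therefore cannot depend on the assigned arm, and removing such people does not favour either arm systematically.

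**Missing follow-up.** At 30% dropout, 0.30 × 198 = 59.4, so about 59 participants would lack a 6-month value. The mixed model and standard chained-equations imputation both treat these values as missing at random.

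**The case against.** The strongest reply is that the plan is sounder than its wording. Intention-to-treat with multiple imputation is the stated preference, the mixed model uses all observed visits, participants with incomplete follow-up are kept, and the analyst is blinded. All of this stands. It means that the following stronger readings are not supported.

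- **That the primary result becomes a completers analysis.** A reader might infer this from the conditional wording. No section names such an analysis, and the model and retention rule point the other way. Blinding also limits, though it does not remove, the scope to choose a method for its result.
- **That the wording costs a known amount of effect.** A reader might reason that if completers gain 10 min/day and intervention dropouts gain nothing, the effect in all randomised is 10 × (1 − loss), that is 8, 7 or 6 min/day at 20%, 30% or 40% loss. That describes informative dropout. A mandatory missing-at-random analysis would also report about 10, so the gap does not measure the conditional wording. The 40% case also exceeds the plan's own dropout figure.
- **That the weekend mismatch biases the comparison.** It rests on a pre-randomisation measurement, so it does not.

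One further reply has force. Valid baseline data could mean only the entry check, which every randomised participant has passed. On that reading nobody leaves the analysis set, but the Primary outcome rule still discards the baseline accelerometer value of anyone in the third row, and the article does not say whether it is then imputed. The sections need reconciling on either reading.

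**Conclusion.** The point holds as an inconsistency of modest size. Followed as written, the protocol article can drop randomised participants whose baseline has four or five valid weekdays and no valid weekend day, and it makes intention-to-treat conditional without need. With 80-95% of days valid, independent days and equally good weekend wear, about 0.2-3% of those randomised are affected, roughly 0.5 to 6 of 198; the number rises if weekend wear is worse. The consequence is a small loss of precision and an analysis set that is not fully intention-to-treat. It is not differential bias, and the documents do not show that the primary estimate would be moved by any stated amount.

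Outcome-related dropout is a separate and remaining uncertainty. Neither the named model nor standard imputation addresses it, and removing the condition would not either. It justifies a sensitivity check, not a claim that the primary analysis is wrong.

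**What to change.** 1. Reconcile Procedure, Primary outcome and Statistical analyses so that every randomised participant is analysed in the assigned arm. State that a baseline with four valid days and no weekend day is either used as recorded or imputed, and choose one.
2. Remove the if-possible condition, and name in advance which missing-data approach is primary. Either the mixed model on all observed data or multiple imputation would serve.
3. Label any completers analysis as supportive only.
4. Add one control-based imputation run for intervention-arm dropouts, as a check on the missing-at-random assumption.

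Items 1 to 3 are wording changes and item 4 is a short additional analysis. No new data are needed. The Trial status section reports recruitment complete and follow-up still running for a small number of participants at version 3.0, so the change should be recorded before the allocation is revealed to the analyst.

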## Discussion

The current trial presents a unique opportunity to study the effectiveness of a new generation of digital interventions that use reinforcement learning (i.e. contextual bandit) in combination with real-time data to deliver a highly personalised app-based digital assistant for promoting physical activity [23]. By addressing the limitations of existing conversational agents and applying advanced machine learning techniques, we aim to pave the way for more effective and adaptable interventions. There is an ongoing proliferation of health and physical activity smartphone apps, yet very little work has been carried out to study the utility and effectiveness of these population-targeted apps [68]. Soon, many more of these apps will also be applying various form of machine learning techniques to influence health behaviour. As such, our work will contribute to understanding how effective these approaches are, and what potential downsides might be. We expect that the current study’s findings will provide increased insights into the benefits of applying machine learning in engaging and retaining participants in app-based interventions, something previous interventions have struggled with [69, 70]. Higher participant engagement and retention have been shown to result in higher levels of behaviour change, and ultimately this will lead to improved health outcomes [70].

There are several strengths to this trial; for example, our trial will have more participants and measure intervention outcomes over a longer period than most comparable interventions in this space [18–21]. Additionally, our trial applies a robust study design, rigorous participant screening, device-measured physical activity outcomes, numerous measures to assess secondary outcomes, standardised exposure and contact across groups, and sufficient analytical power to observe between group changes. The lack of face-to-face contact with participants aligns with the nature of real-world digital interventions and allows the recruitment of participants anywhere in Australia, which enhances the generalisability of the study findings. However, a potential downside of this is a lower feeling of accountability towards study participation and higher levels of attrition. Nevertheless, this study and the intervention it aims to evaluate are well-positioned to generate new knowledge and advance the field in this space.

## Trial status

Protocol version 1.0, September 2024. Currently, the trial is ongoing and recruitment of participants continues. Recruitment began on 5 August 2024 and was expected to be completed by late October 2024.

Protocol version 2.0, February 2025. Currently, the trial is ongoing and recruitment was completed on 25 November 2024.

Protocol version 3.0, June 2025. Currently, the trial is ongoing for a small number of participants, i.e. those that were recruited early on have already completed their participation.

## Data Availability

Upon study completion, only named study investigators will have access to the final trial dataset. While the data will not be publicly available, reasonable requests for access will be considered by the lead investigator (CV) in line with (additional) ethical approvals.
